### Endpoints

*Primary Endpoint*: The primary endpoint is the difference between treatments in change of eGFR over 12 months.

*Secondary Endpoints*: Secondary endpoints are defined as:

• Change in eGFR at 2, 6 and 12 months.

• Difference between treatments in change of eGFR over 2 and 6 months.

• Difference in eGFR slope between pre-treatment and post treatment time points at 2, 6 and 12 months.

• Change of renal function based on the eGFR slope change between pre-treatment and post-treatment at 2, 6 and 12 months (i.e. improvement, stabilisation, failure).

• Ratio of average Resistance Index (RI) at baseline, 6 and 12 months. Intra-renal Resistance Index is defined and calculated by the following formula: Intra-renal RI = (Peak Systolic Velocity-End Diastolic Velocity)/Peak Systolic Velocity.

• Degree of restenosis at 6 and 12 months.

• Clinical events overall: renal or cardiac death, stroke, myocardial infarction, hospitalisation for congestive heart failure, progressive renal insufficiency (i.e. need for dialysis), need for permanent renal replacement therapy, and need of target vessel revascularisation (TVR) or target lesion revascularisation (TLR) at 2, 6 and 12 months, and 3 years.

• Clinical events renal: renal death according to ICD 10, progressive renal insufficiency (i.e. need for dialysis), need for permanent renal replacement therapy, and need of TVR or TLR at 2, 6 and 12 months, and 3 years.

• MACCE: cardiac death, stroke, myocardial infarction, hospitalisation for congestive heart failure at 2, 6 and 12 months, and 3 years.

• Technical success, defined as successful access and deployment of the device with appropriate lesion coverage, stent positioning and patency determined by angiography.

• Acute procedural success, defined as residual percent diameter stenosis <30% by quantitative computerised angiography.

• Procedural success, defined as successful lesion crossing and stent positioning without the occurrence of a serious adverse event up to the moment the introducer sheath is removed,

• Average systolic and diastolic blood pressure (i.e. ambulatory 24 h-BP) at baseline, post procedure, 2, 6 and 12 months.

• Change in average systolic and diastolic blood pressure (i.e. ambulatory 24 h-blood pressure monitoring) at 2, 6 and 12 months.

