### Sample Size Calculation, Statistics, and Calculations

#### Sample Size Calculation

The primary endpoint is the difference between treatments in change of eGFR over 12 month. For this endpoint the intention-to-treat population (ITT) will be taken for primary analysis.

Definitions:

• Controls expectation value μ_C_, variance σ_C _^2 ^and group size n_C _= Medication

• Treatment expectation value μ_T_, variance σ_T _^2 ^and group size n_T _= Medication and Stent

A two-sided test will be performed.

• Null hypothesis: H_0_: μ_T _= μ_C_

• Alternative hypothesis: H_A_: μ_T _≅. μ_C _(↔.μ_T _< μ_C _or μ_T _> μ_C_)

• Minimum difference: Δ = μ_T _- μ_C_

• Variances: σ_T _^2 ^and σ_C _^2^

• Level of significance: α

• Statistical power: 1 - β

• Sample size: N = n_T _+ n_C_

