##### Calculations

The sample size (N) has been calculated using the methods of Bock J, 1998 [22] and Chow

SC, 2003 [23], N = nT + nC. 4 (u1.α/2 + u1.β)2 (σ/Δ)2 for σC 2 = σT 2 = σ2

The probability for incorrect rejection of H0 for a two-sided test (α/2 = 0.025) is u1-0.025 = 1.9600.

The probability for correct rejection of H0 (1-β = 80%) is u0.8 = 0.8416.

Based on published data [24], the estimated GFR difference between baseline and 12 month follow-up in patients with unilateral RAS>70% is 4.35 ml/min. Moreover, from the DRASTIC study [25] considering the patient population with bilateral stenosis the estimated GFR difference at 12 months was 10.0 ± 16 ml/min. Furthermore, in a usual patient population the proportion of patients with bilateral RAS is 15% to 20%. This leads to a calculated increase of estimated ΔGFR for a mixed cohort of patients with unilateral and/or bilateral RAS of approximately: ΔeGFR = 0.2*10+0.8*4.35 ≈ 5.5 ml/min μ_T _= 5.5 ml/min.

In addition, for the medication group, we can assume an eGFR difference or decrease of

μ_C _= -1.0 ml/min at 12 months follow up.

The relevance level is assumed to be 20% of the difference between the therapy and medication or control group. Therefore, the sample size can be calculated as shown in Table 1.

**Table 1 T1:** Calculation of sample size

**Expectation value**			**Relev**.	**Variance^1/2^**			**Sig. level**	**Statistical**	**Sample**
			
**Therapy**	**Ref**.	**Min. diff**.	**level**	**Therapy**	**Ref**.	**k **=	**1-sided**	**power**	**size**
**mue_T_**	**mue_C_**	**Delta**	**delta**	**sigma_T_**	**sigma_C_**	**n_T_/n_C_**	**alpha = 0.05**	**1-beta**	**N = n_T_+ n_C_**

5.5	-1.0	6.5	2.0	14.0	14.0	1.50	1	0.80	**250**

Considering a drop-out rate of approximately 20%, and a PTRAS rate of 20% of patients being initially randomised to BMT group, a total of 300 patients will be enrolled, 150 patients per group. A study patient that has been withdrawn from the study will not be replaced. It is intended to include between 6 and 24 patients per centre.

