### Secondary endpoints

#### Improvement or stabilisation of renal function

The improvement or stabilisation of the renal function will be determined by change in eGFR at baseline/before start of treatment and 12 months after start of therapy. The following definitions will be used to assess the outcome on the renal function for comparison of the stent plus best medical therapy and the best medical therapy alone group [26]:

• Improvement: Increase of the absolute value of the eGFR after treatment by equal or more than 10% compared to the baseline value

• Stabilisation: Absolute value of the eGFR within ± 10% of the baseline value

• Failure: Decrease of the absolute value of the eGFR after treatment by equal or more than 10% compared to the baseline value.

GFR can be estimated by including serum creatinine with other demographic measurements in a prediction equation. These equations are valid only if the renal function is in a steady state, which can be defined by a constant serum creatinine in a given time interval. The eGFR will be calculated according to the following Modification of Diet in Renal Disease (MDRD) Study Prediction equation: eGFR (ml/min/1.73 m2) = 170 × [serum creatinine, mg/dL]^-0.999 ^× [age in years]^-0.176 ^× [0.762 if female] × [1.180 if black] × [serum urea nitrogen, mg/dL]^-0.17 ^× [serum albumin, g/dL]^+0.318^

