### Statistical Analyses

All patients will be analysed on an intent-to-treat basis. Data analysis will be performed on all patients who meet the eligibility requirements of this study using descriptive methods. Discrete variables will be presented as counts and percentage of the total. Continuous variables will be presented as mean ± standard deviation. In case of relative likelihoods the exact one-sided confidence interval of 95% will be calculated.

For the confirmatory analysis of relative likelihoods a binominal test will be performed. For the confirmatory analysis of metric data a t-Test will be performed. If a Kolmogorov-Smirnov-Test shows the data are not normally distributed, a non-parametric Wilcoxon-Test or in case of an inter-individual comparison of 2 datasets a Mann-Whitney-U-Test will be performed.

It is intended to perform the following sub analyses:

- Analysis by treated lesion,

- Analysis including time points after receipt of the Dynamic Renal stent during the study from patients initially randomised to the no revascularisation group.

Other subgroup analyses will be specified in the statistical analysis plan.

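### The only confirmatory test named for proportions is a one-sample binomial test with no reference rate, which does not fit the secondary proportion endpoints compared between arms

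*Protocol article*

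**What the plan says.** The Statistical Analyses section of the protocol article has one sentence on testing proportions: "For the confirmatory analysis of relative likelihoods a binominal test will be performed". The preceding paragraph, on descriptive methods, adds: "In case of relative likelihoods the exact one-sided confidence interval of 95% will be calculated". No reference rate is stated there or anywhere else in the article, and no two-sample test for proportions is named.

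For metric data the same section does make the between-patient case explicit: "in case of an inter-individual comparison of 2 datasets a Mann-Whitney-U-Test will be performed".

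The section on improvement or stabilisation of renal function sorts patients into improvement, stabilisation or failure and says the definitions serve "for comparison of the stent plus best medical therapy and the best medical therapy alone group". Combined clinical events (overall, renal, MACCE) and blood-pressure benefit are also yes/no outcomes available in both arms.

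Two kinds of endpoint fall outside this point. The primary endpoint is metric: "The primary endpoint is the difference between treatments in change of eGFR over 12 months". Some success rates exist only in the stent arm, for example: "Technical success, defined as successful access and deployment of the device with appropriate lesion coverage".

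**The concern.** A binomial test takes its null distribution from Binomial(n, p0), with p0 fixed in advance. The between-arm question is whether p_T = p_C when both rates are estimated from the trial. With no p0 supplied, an analyst who follows the sentence literally has to find one. The two obvious choices are the observed control rate, or one half for the split of all events between equal arms. Neither produces the null hypothesis p_T = p_C for proportions, and they err in opposite directions.

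This is a matter of a stated method, not of detail left to an unseen analysis plan. A test is named, it is called confirmatory, and it is the only one given for proportions. What that section expressly defers to the statistical analysis plan is further subgroup analyses. At stake is whether p-values for renal response and clinical events can be read at their nominal level.

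**Working it through.** The plan states no error rate, power or event rate for any proportion endpoint, so there is no figure of its own to reproduce here.

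**Inputs**
- Patients per arm: 250 evaluable patients (Patient population section) in a 1:1 trial, so 250/2 = 125. The enrolled number is 150 per group.
- Nominal level: two-sided 5%, taken as a working convention.
- Event rates: not in the document. Rates of 10%, 20%, 30% and 50% are assumed.

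**Method.** All pairs (x_T, x_C) of event counts were enumerated and weighted by the product of two binomial distributions. Three tests were applied to each pair:
- (a) exact binomial test of x_T out of n against p0 = x_C/n, as if that were known (p-value is double the smaller tail);
- (b) exact binomial test of x_T out of x_T + x_C against 0.5;
- (c) two-sample chi-square test without continuity correction.

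**False-positive rate, no true difference, 125 per arm**

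| True rate in both arms | (a) control rate as p0 | (b) split against 0.5 | (c) chi-square |
|---|---|---|---|
| 10% | 14.2% | 2.2% | 5.0% |
| 20% | 14.7% | 2.0% | 4.9% |
| 30% | 14.9% | 1.3% | 5.0% |
| 50% | 14.6% | 0.4% | 5.0% |

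The size of (a) depends a little on how the exact two-sided p-value is defined. The minimum-likelihood version gives 14.9% to 16.7% for true rates of 5% to 70% with 125 or 150 per arm.

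**Why (a) is too high.** The test uses variance p(1−p)/n for the difference, but the true variance is 2p(1−p)/n because the control rate is also estimated. The cut-off of 1.96 therefore acts as 1.96/√2 = 1.386, and 2 × (1 − Φ(1.386)) = 16.6% in large samples.

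**Why (b) is too low.** Given S events, the test uses variance S, about 2np, for x_T − x_C. The true variance is 2np(1−p). The cut-off acts as 1.96/√(1−p). At p = 10% this is 2.07, or about 3.9%. At p = 50% it is 2.77, or about 0.6%. Discreteness brings the exact values down to 2.2% and 0.4%.

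**Power, 125 per arm, two-sided 5%**

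| True rates | (b) split against 0.5 | Fisher | Chi-square | Loss, (b) against chi-square |
|---|---|---|---|---|
| 10% vs 20% | 47% | 54% | 60% | 13 points |
| 35% vs 50% | 38% | 62% | 67% | 29 points |
| 50% vs 68% | 39% | 79% | 83% | 44 points |

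For still rarer events, (b) comes close to Fisher's exact test: 71% against 72% for 3% vs 12%, and 66% against 70% for 5% vs 15%.

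**The case against.** The strongest reply is that the phrase may be loose shorthand for comparing two binomial proportions. The next sentence of the section names a t-test equally tersely, without saying one-sample, paired or two-sample, and nobody would read that as one-sample. On that reading neither harm arises. This stands as a limit on the conclusion: the article specifies neither procedure (a) nor procedure (b), so no definite error rate can be attributed to the plan. It does not remove the point. The t-test has a familiar two-sample form under the same name, whereas the binomial test by that name is a one-sample test. The section also spells out the between-patient case for metric data and gives no counterpart for proportions.

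Three stronger readings are tempting and not supported:

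- *That every proportion endpoint is mis-tested.* Technical, acute procedural and procedural success have no comparator, and a one-sample method is the right type for them, although no reference rate is given.
- *That the trial's main result is at risk.* The primary endpoint is a metric change in eGFR and goes to the t-test or its rank alternative. Neither that test nor the sample size depends on this sentence.
- *That the one-sided exact interval contradicts two-sided testing.* The statement "A two-sided test will be performed" stands in the sample-size section and concerns the primary endpoint. The interval is in the descriptive paragraph, and a one-sided exact bound is a legitimate summary of a single rate.

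It is also fair to say that the power loss under (b) is small against Fisher's test when events are rare, and that the section does not list which proportion endpoints it regards as confirmatory.

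**Conclusion.** The point holds for the secondary proportion endpoints compared between arms. The article names a one-sample test, supplies no reference rate, and gives no two-sample test for proportions. It is explicit that renal-function category is a between-arm comparison. For clinical events and blood-pressure benefit, the between-arm use follows from their being available in both arms.

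The size is conditional. With 125 per arm and assumed rates of 10% to 50%, the false-positive rate at a nominal 5% is about 14–15% if the observed control rate is treated as known, and 0.4–2.2% if the event split is tested against one half. In the second case the power loss against chi-square is moderate for rarer outcomes and large for common ones. If a two-sample comparison was intended, the effect is nil and only the wording is at fault. The correction is worth making because the sentence leaves room for procedures with very different error rates under a confirmatory label. It does not bear on the primary analysis.

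**What to change.** In the Statistical Analyses section, replace the binomial-test sentence for between-arm proportions with a two-sample test of p_T = p_C on the randomised groups at two-sided 5%: the chi-square test, or Fisher's exact test where events are sparse. Report the risk difference with a two-sided 95% confidence interval, for example Newcombe or Miettinen–Nurminen.

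For the three-level renal outcome, state the dichotomy to be tested (for example failure versus not), or compare all three levels with a chi-square test.

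For technical, acute procedural and procedural success, report the proportion with an exact (Clopper–Pearson) interval and no confirmatory test, since no reference rate is stated.

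The cost is a few lines of text and standard software, with no new data or patients. P-values will be less favourable than if the control rate were treated as known. Fisher's test is somewhat conservative: 2.2% to 4.3% false positives over assumed rates of 5% to 70% with 125 or 150 per arm, against 4.7% to 5.7% for chi-square.

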Renal function is one of the most powerful predictors of survival [40]. Another one is left ventricular hypertrophy [41]; the analysis of the course of left ventricular mass index is also included as a secondary endpoint because the reducing the activation of the renin-angiotensin-aldosterone-system by RAS revascularisation should lead to a regression of left ventricular hypertrophy [41]. Affecting these major endpoints, renal function and left ventricular hypertrophy, RAS stenting should also impact the composite clinical endpoint of patient survival, hospitalisation and end-stage renal failure after 3 years.

Provided a timely initiation of all study sites it is expected to finish patient enrolment within 1 year so that the analysis of the primary endpoint should be available in 2011.

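### The analysis section labels tests of proportions, and of metric data in general, confirmatory, although only the 12-month eGFR change has that standing

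*Protocol article*

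**What the plan says.** Under Endpoints there is one primary: "The primary endpoint is the difference between treatments in change of eGFR over 12 months". The Sample Size Calculation section sets up a two-sided test for it, and no other endpoint receives a hypothesis, an alpha or a power statement.

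Statistical Analyses first describes the approach as descriptive: "Data analysis will be performed on all patients who meet the eligibility requirements of this study using descriptive methods". It then assigns tests by type of data. For proportions: "For the confirmatory analysis of relative likelihoods a binominal test will be performed". For continuous variables: "For the confirmatory analysis of metric data a t-Test will be performed". The only interval named for proportions is one-sided: "In case of relative likelihoods the exact one-sided confidence interval of 95% will be calculated". The section passes other subgroup analyses to the statistical analysis plan. It does not say there which endpoints are confirmatory.

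The proportions are all in the secondary list. Three clinical-event composites (overall, renal, MACCE) each carry four time points, for example "MACCE: cardiac death, stroke, myocardial infarction, hospitalisation for congestive heart failure at 2, 6 and 12 months, and 3 years". The Clinical events section adds the individual events.

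**The concern.** A confirmatory label tells readers that a significant result may be claimed at its nominal error rate. No proportion in this trial has that standing by design, so the sentence on proportions can refer only to secondary endpoints. The sentence on metric data covers the primary, but also blood pressure, left ventricular mass, kidney size and other secondaries. The descriptive wording just before it points the other way, so a reader cannot tell which results were meant to carry a controlled claim.

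At stake is the case of a null or borderline eGFR result. An author could then present a significant secondary comparison, such as one event composite at one visit, as confirmatory and cite the published protocol for it.

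**Working it through.** **1. Which endpoints could the label cover?**

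| Type of data | Endpoints listed | Standing |
|---|---|---|
| Metric | 12-month eGFR change | primary |
| Metric | eGFR at other visits, eGFR slope, 24-hour blood pressure, ventricular mass index, kidney size, quality of life | secondary |
| Proportion | three event composites, individual events, renal-function categories, procedural success measures | secondary |

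No proportion is primary, so for proportions the label has no primary endpoint to apply to.

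**2. The plan's own figures.** The article gives no error rate for any secondary endpoint, so there is none to reproduce. Its only design calculation concerns eGFR. Table 1's total of 250 reproduces with one-sided alpha 0.05, allocation 1.5, SD 14 and a difference of 6.5 − 2.0 = 4.5:

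N = (2.5²/1.5) × (1.645 + 0.842)² × (14/4.5)² = 249.3, rounded up to 100 + 150 = 250.

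The one-sided alpha in Table 1 conflicts with the two-sided test in the text. That is a separate matter, but it is a reason to state the sidedness when the confirmatory test is named. The text's two-sided 5% corresponds to 2.5% in favour of stenting.

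**3. What would confirmatory secondary tests imply?** Inputs from the article: 3 composites × 4 time points = 12 comparisons. Assumptions, not in the article: each is a between-arm test at two-sided 5%, there is no true effect, and the test statistics are normal with common correlation ρ.

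- Independent tests, favouring stenting: 1 − (1 − 0.025)¹² = 0.262.
- Independent tests, either direction: 1 − (1 − 0.05)¹² = 0.460.
- Correlated tests, favouring stenting: 1 − ∫ Φ[(1.96 − √ρ·u)/√(1 − ρ)]¹² φ(u) du. For either direction, the bracketed probability is replaced by that of lying between −1.96 and +1.96 given u.

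| ρ | Favouring stenting (nominal 2.5%) | Either direction (nominal 5%) |
|---|---|---|
| 0 | 26% | 46% |
| 0.5 | 16% | 32% |
| 0.8 | 9% | 19% |

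**4. Cross-check with realistic dependence.** Events were simulated for 150 patients per arm with equal rates in both arms. They were counted cumulatively at months 2, 6, 12 and 36, with the overall composite formed as the union of the renal and MACCE events. The 3-year rates were assumed (renal 10–30%, MACCE 20–40%). The 12 z-tests gave 15–17% favouring stenting and 29–33% in either direction, close to the ρ = 0.5 row. A second simulation, built from assumed component rates, gave 16% favouring stenting with z-tests and about 10% with Fisher's exact test.

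**The case against.** The strongest reply is that the word is used loosely. Because the preceding text is descriptive, it may mean no more than inferential, and the section is a list of tests by data type. It does not say that every secondary endpoint or every time point is tested, or at what level. A binomial test paired with an exact one-sided interval is usually a one-sample procedure, so between-arm comparisons of event rates may not be meant. Technical and procedural success exist only in the stent arm and allow no between-arm claim. The Discussion and Conclusion rest the expected significant result on eGFR alone. All of this stands, and it is why the rates above are conditional.

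The absence of a testing order or alpha split for secondaries is also no fault here, since a condensed article commonly leaves it to the full protocol or the analysis plan.

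One part of the reply does not succeed. The point rests on something the article states, not on something it omits. An analysis plan that called the secondaries exploratory would contradict the published sentence.

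A reader might go further and infer that a false confirmatory claim for stenting is likely. The article does not support that. For the 12 composite comparisons, the chance favouring stenting stays at about a quarter or less at two-sided 5%, and the larger figures of 32% and 46% include errors against stenting. Higher rates need a longer list of tests than the article says will be run. Nor does the Discussion's remark that "RAS stenting should also impact the composite clinical endpoint of patient survival, hospitalisation and end-stage renal failure after 3 years" make that composite confirmatory: it is rationale, and the composite matches none of the three event families defined under Endpoints.

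**Conclusion.** The point holds as a misstatement in Statistical Analyses: a confirmatory label is attached to a class made up only of secondary endpoints, and to metric data without restriction, while the design supports one confirmatory test. If the label were acted on for the three event composites at all four time points, the false-positive risk favouring stenting would be roughly four to ten times nominal (9.3/2.5 = 3.7 at ρ = 0.8; 26.2/2.5 = 10.5 under independence). This rests on assumed two-sided 5% between-arm tests at every listed time point. The defect in wording does not depend on those figures. It leaves the primary analysis untouched and should be corrected before results are reported.

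**What to change.** In Statistical Analyses, replace the two sentences on confirmatory analysis with wording to this effect: the only confirmatory test is the two-sided 5% comparison of 12-month eGFR change. All secondary endpoints, their time points and the sub-analyses are exploratory and will be reported with estimates and 95% intervals. The choice of test by data type can stay, without the label.

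If the sponsor wants one confirmatory secondary claim, name a single endpoint at a single time point (for example the overall clinical-event composite at 3 years) and test it only if the primary is significant. This keeps the overall error at 5%.

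The change costs two sentences and needs no extra patients or data. The downside is that secondary results, other than any one so named, can no longer be called confirmatory.
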